Understanding and assessing DFA in children are important for delivering successful dental care with high satisfaction in this age group. Among the vast number of assessment method options available today, self-report assessment, parental proxy assessment, observation-based assessment, and physiological assessment are the 4 major types for DFA in children [11]. In the recent literature, salivary alpha-amylase, an enzyme correlated with both adrenaline and noradrenaline, has also been used as a marker for autonomic nervous system activity and stress [12].

Factors in the dental setting that trigger DFA include the loud sounds of dental instruments, presence of strangers examining the oral cavity, and the fear of pain [13]. Of these, the biggest trigger of DFA is the anticipation and use of local anesthesia injections [5,13]. Although necessary to provide adequate pain control during certain treatments, local anesthesia injections are understandably uncomfortable [5]. For children, the initial injection combined with the feeling of numbness during the procedure is especially distressing [5]. Pharmacological agents, combined with light to moderate sedation, or general anesthesia can also be considered for noncooperative patients; these options are often time-consuming and confer a higher cost as well as health risk [1]. In the current literature, audiovisual distractions such as tablets or TV screens have been used as additional distraction techniques rather than just traditional tell-show-do distraction, with overall positive results [14]. However, there is a lack of interactivity with these techniques, and as a result, they produce less immersive environments with distraction for the children [15]. Lack of patient cooperation due to DFA often obliges dentists treating pediatric populations to end appointments prematurely and sometimes without completing the planned procedure. Treating an anxious and fearful patient can create an environment of stress for the clinician and associated dental team [1].

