### Sample and Setting

This pilot will include 20 participants, totalling 10% of the expected 200 children to be included in the final study. All participants in this pilot study will be allocated in an equal ratio of 10 per group. Recruitment will be carried out at the dental clinic of the Centre Hospitalier Universitaire Sainte-Justine, a pediatric hospital in Montreal, Canada. This clinic mostly serves patients with SHCN such as craniofacial abnormalities, autism spectrum disorder, cancer, and others. Pediatric patients with SHCN represent around 80% of the total clientele of this clinic, while the rest is comprised of otherwise healthy patients with dental traumas and other dental emergencies.

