### Statistical Analysis

Analysis will be conducted using the SAS (SAS Institute) statistical analysis software (version 9.4). Descriptive statistics, by treatment, will be conducted for demographic and clinical variables and will be used to present sociodemographic and clinical data, parent and health care professional satisfaction levels, and procedural time. Due to a small sample size, we will also assess effect sizes.

For the pilot project, we plan to perform descriptive analyses of the sample as well as comparative analyses between the 2 groups. Nonparametric tests for procedural type, age, parental presence, parental and health care satisfaction levels, and baseline (T0) anxiety score measurement will be used to assess the composite outcome for mean salivary cortisol level and mean difference in anxiety score (using the Venham Clinical Cooperation Scale and Venham Clinical Anxiety Scale) between the experimental and control groups at T2. Analyses will be carried out according to the intention-to-treat principle, with a significance level (α) of .025, considering Bonferroni's correction.

For secondary outcome analyses, nonparametric tests adjusted for procedural type, age, and parental presence will be used to assess the mean procedural length at T2 using the VAS and 6-item tailored questionnaire, respectively. Comparison of dichotomous variables including the necessity for procedural retakes, use of other nonpharmacological interventions, and the occurrence of side effects will be assessed using the Cochran-Mantel-Haenszel test.

The study data will be recorded in the REDCap system belonging to URCA. The data manager associated with URCA and independent of the study will be responsible for the storage of the recorded data. However, a URCA biostatistician independent of the study will be responsible for the data analysis. The data analysis plan will be discussed with the principal investigator ([name]). Interjudge correlations will be conducted for the video tape analysis. Two judges will independently rate the anxiety measure on the videotapes. Subsequently, we will conduct intraclass correlation coefficient analyses to compare the scores for each of the recruited patients between the 2 judges.

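### Six variables, two of them outcomes measured at T2, are listed for the anxiety comparison in 20 children; adjusting for all six can cost precision and remove part of the treatment effect

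*Protocol article*

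**What the plan says.** The second paragraph of Statistical Analysis (protocol article) describes the T2 comparison of anxiety between arms: "Nonparametric tests for procedural type, age, parental presence, parental and health care satisfaction levels, and baseline (T0) anxiety score measurement will be used". That is six variables: type of procedure, age, whether a parent is present, parental satisfaction, professional satisfaction, and anxiety at T0. The analysis is by intention to treat, "with a significance level (α) of .025, considering Bonferroni's correction".

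The sentence speaks of tests for these variables. The next paragraph, on secondary outcomes, is explicit about adjustment: "nonparametric tests adjusted for procedural type, age, and parental presence will be used to assess the mean procedural length at T2".

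Other sections bear on the list:

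- **Sample and Setting**: "This pilot will include 20 participants, totalling 10% of the expected 200 children to be included in the final study", and "All participants in this pilot study will be allocated in an equal ratio of 10 per group".
- **Study Time Points**: both satisfaction measures are taken at T2.
- **Objectives** and **Primary Outcomes**: satisfaction is to be compared between the arms and is one of the primary outcomes.
- **Measures of Primary Outcomes**: the parental question asks, among other things, about relief of the child's anxiety by the intervention received. Professional satisfaction consists of two scores, a VAS and a 6-item total.
- **Study Proceedings Including Data Collection**: staff, children and parents cannot be blinded.

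**The concern.** Each adjuster uses a degree of freedom and adds chance collinearity with the arm. In a large trial this is negligible. With 10 children per arm it is not, and adjustment pays only if the covariates explain enough of the outcome to cover the cost. The protocol gives no reason to expect that from six variables.

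The list also mixes two kinds of variable. Procedure type, age and T0 anxiety are fixed before treatment starts, and parental presence is a feature of the visit. The two satisfaction measures follow treatment, are given by people who know the allocation, and may move with both the arm and the child's anxiety. Holding them constant means comparing VR and TV among children whose parents and dentists were equally satisfied. That is not the effect of VR.

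At stake is the preliminary anxiety effect, which the protocol intends as groundwork for a larger trial. It could come out less precise than a raw comparison, or too small.

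**Working it through.** **Inputs from the protocol.** N = 0.10 × 200 = 20, 10 per arm, which reproduces the stated size. α = 0.05/2 = 0.025, which reproduces the stated level for two tests. Sidedness is not stated; two-sided is assumed. Six variables are listed. The protocol gives no standard deviation, effect size or covariate R².

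**Cost of adjustment.** This is a linear-model approximation to the rank-based method, which is not named. For p one-degree-of-freedom covariates that are independent of arm:

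- residual degrees of freedom = 18 − p
- expected variance inflation of the arm contrast = (N − 3)/(N − 3 − p) = 17/(17 − p)
- variance relative to no adjustment = (1 − R²) × 17/(17 − p)
- break-even R² = 1 − (17 − p)/17 = p/17

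| Adjusters | p | Residual df | Inflation | Break-even R² | Counting the t quantile |
|---|---|---|---|---|---|
| T0 anxiety only | 1 | 17 | 17/16 = 1.06 | 6% | 7% |
| T0 anxiety + one two-level variable | 2 | 16 | 17/15 = 1.13 | 12% | 14% |
| Four listed variables without satisfaction | 4 | 14 | 17/13 = 1.31 | 24% | 27% |
| All six, one df each | 6 | 12 | 17/11 = 1.55 | 35% | 41% |

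For p = 6 the t quantile at .9875 rises from 2.445 (18 df) to 2.560 (12 df). If the covariates explain nothing, the interval is √1.545 × 2.560/2.445 = 1.30 times as wide. The last column for p = 6 is 1 − 1/1.302² = 0.41. For p = 2 the width ratio is 1.077, and 1 − 1/1.077² = 0.14.

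**What it means for the detectable effect** (80% power, two-sided α .025, noncentral t; R² assumed):

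| Model | R² | Relative variance | Detectable effect |
|---|---|---|---|
| Unadjusted | – | 1.00 | 1.48 SD |
| Six covariates | 0.25 | 0.75 × 1.545 = 1.16 | 1.66 SD |
| Six covariates | 0.49 | 0.51 × 1.545 = 0.79 | 1.37 SD |
| T0 only | 0.25 | 0.75 × 1.0625 = 0.80 | 1.33 SD |
| T0 only | 0.49 | 0.51 × 1.0625 = 0.54 | 1.10 SD |

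Six covariates therefore lose at R² = 0.25 and gain at R² = 0.49. At equal R², T0 alone does better.

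**The satisfaction measures.** The formula above assumes covariates unrelated to arm, which satisfaction need not be. A separate check used simulation (5,000 runs per setting) under these assumptions:

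- a true effect of −1 SD;
- T0–T2 correlation ρ of 0.3, 0.5 or 0.7;
- two T2 satisfaction scores, each equal to −0.5 × T2 anxiety plus independent noise of variance 0.75;
- three further covariates carrying no information.

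In this setting the share of the effect that survives adjustment is 1/[1 + (1 − ρ²) × 2 × 0.25/0.75]. That gives 1/1.607 = 0.62, 1/1.5 = 0.67 and 1/1.34 = 0.75. The simulated estimates agree: −0.62, −0.66 and −0.75. Power was 0.18, 0.22 and 0.37, against about 0.44 unadjusted. With T0 alone the estimate stayed at about −1.0 and power was 0.44, 0.53 and 0.71. The sampling variance of the six-variable estimate (0.11 to 0.19) was no larger than the unadjusted one (about 0.20), so in this scenario the harm was bias, not imprecision.

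**The case against.** The strongest reply has four parts.

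1. **The loss is conditional.** It depends on an R² that the protocol does not give, and at R² = 0.49 six covariates gain. This stands. A reader might infer that 20 children cannot carry six adjusters at all, or that precision is certain to fall. The documents support only that it can fall, with break-even at about 35 to 41%.
2. **The inflation formula does not fit the satisfaction measures.** This also stands. The 1.55 describes six baseline-type covariates. The case against the two satisfaction variables rests on their timing and their role as outcomes. Without them the listed set gives 1.31 and a break-even of 24%, which T0 anxiety alone would reach at a correlation of about √0.235 = 0.49.
3. **Coding is a matter for the analysis plan.** Procedure type in four classes and both professional scores would give nine degrees of freedom and an inflation of 17/8 = 2.13. The protocol fixes neither choice, so that figure is not relied on here.
4. **The wording says tests for, not adjusted for, and this is a pilot.** Adjustment is the likelier reading because the next paragraph uses that term with three of the same variables, but it is not certain. The anxiety objective is preliminary, which limits the consequence.

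A reader might also fault the procedure-length analysis for leaving out T0 anxiety, since the Introduction says "Lack of patient cooperation due to DFA often obliges dentists treating pediatric populations to end appointments prematurely". The documents do not support that. The omission contradicts nothing and has no bearing on the anxiety contrast, and the sentence does not settle whether anxious children have longer or shorter procedures. Added to the three adjusters listed there, T0 anxiety would change the variance by (1 − r²) × 14/13. That is −2%, −10% or −19% for an assumed partial correlation of 0.3, 0.4 or 0.5, and a loss when r is below √(1/14) = 0.27. It is an optional addition.

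**Conclusion.** The point holds for the anxiety comparison. Read as adjusters, the six variables leave 12 residual degrees of freedom and inflate the variance of the arm contrast by about 1.55. Adjustment then loses precision unless the six jointly explain more than about 35% of the variance (41% with the t quantile), and nothing in the protocol suggests that they do. The graver fault is that two of the six are primary outcomes measured after unblinded treatment. They cannot count as baseline precision, and under the assumed correlations they removed a quarter to over a third of a 1 SD effect.

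This rests on reading the sentence as adjustment, on one degree of freedom per variable, on a linear approximation to an unnamed rank method, and on a two-sided α of .025. The size of the bias rests on assumed correlations. That satisfaction is measured at T2 and is an outcome is stated in the protocol. No fault is found in the secondary adjuster list.

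**What to change.** In Statistical Analysis, for the T2 anxiety comparison:

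- State that the comparison is adjusted for the T0 Venham score and at most one other prespecified baseline variable, for example a two-level class of the planned procedure. Break-even R² falls to 2/17 = 12% (14% with the t quantile).
- Remove parental and professional satisfaction from the adjusters and compare them between arms as outcomes only.
- Show age, parental presence and finer procedure types by arm, descriptively.

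The same set should not be imposed on every comparison. Side effects and satisfaction have no T0 value. For the Cochran-Mantel-Haenszel tests, a 0 to 5 score crossed with two procedure classes gives up to 6 × 2 = 12 strata for 20 children.

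The cost is a change of wording, with no new data. The downside is that age, in a sample aged 6 to 17 years, and finer procedure types are no longer adjusted for, so a chance imbalance in them would be visible in the tables but not corrected.

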### Study Time Points

Sociodemographic data will be assessed before the intervention at baseline (T0) to establish a baseline using a simple questionnaire completed by the parent or legal guardian present while sitting in the waiting room. Salivary alpha-amylase samples will be collected at T0 and after the intervention/procedure (T2; Multimedia Appendix 1). Measures of specific dental procedure–related anxiety and uncooperative behavior will be assessed at T0, during the procedure (10 minutes from the start; T1), and immediately after the end of the procedure (T2). Physiological parameters will be measured at T0, during the intervention (T1), and T2. Data on occurrence of side effects will be assessed and monitored at all times for the duration of this study. All clinical monitoring will be performed by the dental resident on site. Measures of parent or legal guardian and health care professional satisfaction will be assessed at T2.

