#### Secondary Outcomes

The secondary outcomes will be (1) changes in physiological parameters (such as heart rate and pulse oximetry) during and after the intervention compared with baseline, (2) occurrence of side effects, (3) deviation from the normal procedure length, (4) rescheduling of procedures in the event cooperation is impossible, and (5) salivary amylase levels.

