#### Measures of Secondary Outcomes

The secondary outcomes will be measured as described here. Physiological parameters will be continuously measured using the Nellcor pulse oxygen saturation meter (Covidien), an approved and validated device. The occurrence of side effects will be collected from arrival on site to discharge from the study using a checklist of common side effects experienced while using VR and also related to dental medication. The length of the procedure will be measured and collected for every participant and will be compared with the average duration for a similar procedure that will have been measured prior to the study by the clinic’s personnel. Rescheduling of procedures in the event that cooperation is impossible will be noted. Salivary amylase levels, as a stress biomarker, will be measured before and after the dental procedure as described in the following section.

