#### Measurement of Salivary Amylase

Saliva samples will be collected from all children in this study at 2 different study time periods: before (T0) and after (T2) the intervention. Salivary alpha-amylase has been recognized and validated as a reliable and specific marker for autonomic nervous system activity and has been proposed as an alternative biomarker for stress [12]. Alpha-amylase sampling has been performed in previous studies to evaluate DFA for children undergoing dental procedures [28-30]. Alpha-amylase, as a salivary biomarker, can be considered an important and noninvasive tool for assessment of anxiety-related events, such as dental extraction and other treatment, for children [28,31].

Salivary samples will be collected using a sterile dental cotton swab from under the tongue 10 minutes before and 10 minutes after the procedure and stored immediately within a sterile vile in a research-specific on-site freezer. Samples will be collected by the dental resident and taken to the laboratory. Results will be entered in REDCap for analysis after the study.

Table 1 provides an overview of which questionnaires will be answered by which respondents during the study.

**Table 1 table1:** Questionnaires and corresponding respondents.

Questionnaires	Respondents
Parent or legal guardian satisfaction	Parents or legal guardians
Health care professional satisfaction	Health care professional
Anxiety score, physiological parameters	By proxy through research assistants

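### The leading between-group test names salivary cortisol, but the trial collects only salivary alpha-amylase, so the biomarker comparison cannot be run as written

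*Protocol article*

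**What the plan says.** The Statistical Analysis section of the protocol article describes one comparative analysis before it turns to the secondary outcomes. Nonparametric tests "will be used to assess the composite outcome for mean salivary cortisol level and mean difference in anxiety score", the latter "using the Venham Clinical Cooperation Scale and Venham Clinical Anxiety Scale) between the experimental and control groups at T2". The analysis follows intention to treat, at a significance level of .025 that is said to reflect Bonferroni's correction. The list of factors attached to these tests contains one T0 measurement, the anxiety score.

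The sections on data collection describe a different analyte:

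- Study Time Points: "Salivary alpha-amylase samples will be collected at T0 and after the intervention/procedure (T2; Multimedia Appendix 1".
- Measurement of Salivary Amylase, on the timing of collection: "Saliva samples will be collected from all children in this study at 2 different study time periods: before (T0) and after (T2) the intervention". The section justifies the choice of marker: "Salivary alpha-amylase has been recognized and validated as a reliable and specific marker for autonomic nervous system activity".
- Measures of Secondary Outcomes: "Salivary amylase levels, as a stress biomarker, will be measured before and after the dental procedure as described in the following section".
- Secondary Outcomes: the list ends with "4) rescheduling of procedures in the event cooperation is impossible, and (5) salivary amylase levels".
- Objectives: salivary amylase is secondary objective 5, one of the items to be compared between the VR and TV groups.

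The paragraph on secondary outcome analyses names procedural length and three dichotomous variables (retakes, other nonpharmacological interventions, side effects). It does not name amylase.

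**The concern.** Cortisol and alpha-amylase are different analytes with different assays, so one name cannot stand for the other. The independent biostatistician who is to run the analysis is told to compare a variable that the data collection will not produce. The analyst must then decide, possibly after seeing the data, whether to substitute amylase, drop the biomarker, or treat the composite as the anxiety score alone. Each choice changes what is tested at .025.

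Three further problems sit in the same sentence. A biomarker level and a 0 to 5 behaviour rating are called a composite with no rule for combining them, so the tested quantity stays undefined even after the analyte is corrected. The saliva marker, declared secondary, appears in the comparison that precedes the secondary analyses. And the amylase comparison promised in the Objectives has no named test.

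**Working it through.** **1. Which analyte is named where.**

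| Section of the protocol article | Analyte named |
|---|---|
| Abstract, Methods | salivary alpha-amylase |
| Introduction | salivary alpha-amylase |
| Objectives (secondary, item 5) | salivary amylase |
| Study Time Points | salivary alpha-amylase, T0 and T2 |
| Secondary Outcomes (item 5) | salivary amylase |
| Measures of Secondary Outcomes | salivary amylase, before and after |
| Measurement of Salivary Amylase | alpha-amylase, T0 and T2 |
| Study Proceedings Including Data Collection | salivary alpha-amylase |
| Statistical Analysis | salivary cortisol |

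Cortisol occurs once, in the only sentence that specifies a between-group test for a saliva marker.

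**2. What the .025 can cover.** The overall level is not stated; assume 0.05.

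- Two tests: 0.05 / 2 = 0.025. This reproduces the plan's figure. The pair could be one biomarker plus one anxiety score, or the two Venham scales.
- Three tests (biomarker plus both Venham scales): 0.05 / 3 = 0.0167. This does not match. Three tests at .025 each would sum to 3 × 0.025 = 0.075, or 1 − 0.975³ = 0.0731 if independent.

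The stated level therefore fits two different pairs, and the text does not say which is meant. If amylase moves to its declared tier and the two Venham scales remain, 0.05 / 2 = 0.025 still holds. Correcting the analyte changes neither this figure nor the sample size of 20.

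**3. Side benefit of using the T0 saliva sample.** The sentence names no T0 value for the biomarker, although saliva is taken from every child at T0. The documents give no correlation r between T0 and T2 amylase, so r = 0.5 and r = 0.7 are assumptions. In linear ANCOVA with two arms and a random baseline, the expected variance relative to an unadjusted T2 comparison is (1 − r²) × (1 + 1/(N − 4)). With N = 20 the second factor is 1 + 1/16 = 1.0625.

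- r = 0.5: 0.75 × 1.0625 = 0.797, a reduction of about 20%, equivalent to 1/0.797 = 1.25 times the sample.
- r = 0.7: 0.51 × 1.0625 = 0.542, a reduction of about 46%, equivalent to 1/0.542 = 1.85 times the sample.

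These figures are for a linear model. The plan specifies nonparametric tests, so for a rank-based analysis they are only a guide.

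**The case against.** The strongest reply is that cortisol is a slip for amylase in a 20-child feasibility pilot, and that little depends on it. Parts of this stand. The declared primary outcomes are recruitment, completion of planned procedures and satisfaction, and none of them uses saliva. Both Venham scores can be computed whatever happens to the biomarker. A slip is plausible. But the article does not show that it is one, and the analyst should not have to guess.

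A reader might also infer more than the document supports:

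- *That the trial's primary analysis fails.* It does not. This is the leading comparative test, not the feasibility endpoint.
- *That exactly half the composite is lost.* That holds if the composite has two components. With the Venham scales counted separately it is one of three. If the Bonferroni level signals separate tests, the anxiety comparison runs without the biomarker.
- *That amylase has no analysis at all.* Descriptive statistics by treatment for clinical variables, effect sizes and general comparative analyses could cover it, and a separate analysis plan, not shown, may name a test. The absence of a named test would be no finding by itself. It counts here because the biomarker test that the article does name uses another analyte.
- *That no saliva data will exist.* Saliva is collected from all children and frozen; what is missing is any description of a cortisol assay.

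Finally, baseline adjustment is a separate improvement. Its gain does not measure the size of the contradiction.

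**Conclusion.** The contradiction is real and lies in the current text. It is a wrong statement, not detail left out of a condensed article. The biomarker part of the leading comparison cannot be carried out as written, the composite is undefined, the marker is placed above its declared tier, and the scope of the .025 is unclear. The damage is confined to that sentence: one variable of two or three, with no effect on the feasibility outcomes, the Venham scores or the sample size.

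The conclusion on the analyte rests on the article's text alone; the multimedia appendices are not shown. The reading of .025 assumes an overall level of 0.05. The 20% and 46% variance reductions assume r and a linear model.

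**What to change.** In Statistical Analysis:

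1. Replace mean salivary cortisol level with salivary alpha-amylase at T2. Analyse it as the secondary outcome already listed, adjusted for its T0 value by rank-based (nonparametric) ANCOVA, in keeping with the stated nonparametric plan.
2. Drop the word composite.
3. State the overall significance level and which tests share the .025. If they are the two Venham scales and the overall level is 0.05, the figure stays as it is. Say also that the amylase test lies outside that allowance.

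The cost is one or two sentences. No new data are needed if amylase is the intended marker, as every measurement section indicates. If cortisol was truly intended, the objectives, outcomes and measurement sections would need to add it and describe its assay. In either case the change should be made before the data are analysed.

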### Objectives

The primary research objectives are to determine (1) the feasibility and acceptability of VR distraction for children with special needs requiring dental procedures, (2) compare parent and health care professional satisfaction levels between the VR distraction group and the clinic’s standard mounted TV showing cartoons, and (3) observe the preliminary effects of VR distraction on reducing patient anxiety during dental procedures compared with standard nonpharmacological behavior management.

The secondary objectives of this study are to compare the following between the VR distraction group and the clinic’s standard mounted TV showing cartoons: (1) physiological parameters (pulse and oxygen saturation), (2) the occurrence of side effects, (3) dental procedure length, (4) the number of retakes of dental procedures due to DFA, and (5) salivary amylase levels.

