DFA scores will be evaluated using the Venham Anxiety and Behavioral Rating Scale [23]. It is an observation-based assessment by proxy for DFA and is among the most frequent behavior scoring models for DFA [23] (Multimedia Appendix 4). It is composed of 2 scales used to assess the anxiety and uncooperative behavior of children in the dental setting. The scale is also found under the name Clinical Anxiety Scale/Uncooperative Behaviour Rating Scale or Venham Clinical Cooperation Scale and Venham Clinical Anxiety Scale and has been used as an anxiety rating scale in other studies that have evaluated the efficacy of VR distraction for the management of DFA [11,24,25]. Both consist of a 6-point scale, with 6 defined behavioral levels that range from 0 to 5. The highest score defines the highest anxiety level or lack of cooperation [23]. A high degree of reliability has been observed for both scales, even for an untrained observer [23,26]. The scale points are measured by proxy and anchored in objective, specific, and readily observable behavior. The research assistant indicates the participant’s behavior by picking a number from 0 to 5 according to the scale; thus, for each participant, 2 scores on the levels of anxiety and cooperation with the dental procedure will be obtained at T0, T1, and T2. Venham et al [27] reported that the scale is a reliable and valid scale and provides an interval-level measurement. The scale has been a useful instrument for assessing a child’s response to dental stress. The anxiety score and uncooperative score will both be evaluated at T0 (baseline), during the procedure at 10 minutes after the beginning of the procedure (T1), and after the completion of the procedure (T2). The videos will be reviewed by 2 independent evaluators who will provide a score for the anxiety of each child during the procedure. Scores will be compared afterwards. The same scales will be used during observation of the child’s behavior using the video recordings by a separate member of the team. Both evaluations (when available depending on consent) will allow for inter-rater agreement to be calculated.

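### The only named between-group anxiety comparison is at T2, after the procedure, although the objective is anxiety during it

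*Protocol article*

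**What the plan says.** The Objectives section lists, as the third primary objective, to "observe the preliminary effects of VR distraction on reducing patient anxiety during dental procedures compared with standard nonpharmacological behavior management". Under Experimental Treatment and Study Proceedings, the child plays for as long as the procedure lasts.

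Study Time Points schedules the anxiety and uncooperative-behavior scores at baseline (T0), "during the procedure (10 minutes from the start; T1), and immediately after the end of the procedure (T2"). Measures of Primary Outcomes repeats the schedule: "during the procedure at 10 minutes after the beginning of the procedure (T1), and after the completion of the procedure (T2"). The same section adds that two independent evaluators will score each child's anxiety during the procedure from video, where consent allows.

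Statistical Analysis names one group comparison of anxiety. It joins a mean salivary level and the difference in Venham scores "between the experimental and control groups at T2". The T0 score is among the variables named for the tests: "baseline (T0) anxiety score measurement will be used to assess the composite outcome". Alpha is .025 after a Bonferroni correction. The video ratings are assigned to an intraclass correlation between the two judges.

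**The concern.** The question asked and the contrast tested refer to different periods. Distraction is meant to work while treatment is under way. T2 comes once treatment and distraction have both stopped, so a T2 difference reflects how the child is after release. That may be related to anxiety in the chair, but it is another quantity.

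What is at stake is interpretation. A T2 result with no difference could be reported as VR not reducing procedural anxiety, and a T2 difference as showing that it does; neither follows. The Conclusion section offers the results as preliminary data for a later trial, and the effect size carried forward would describe the post-procedure period. If T1 is chosen only after the data have been seen, the choice is post hoc.

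**Working it through.** No figure in the article bears on this point, so the check sets the sections side by side.

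1. **Target.** Objectives: "observe the preliminary effects of VR distraction on reducing patient anxiety during dental procedures". The period of interest is the procedure itself.
2. **When the intervention acts.** Experimental Treatment and Study Proceedings: for the whole procedure. T1 therefore falls on intervention, and T2 after it.
3. **When anxiety is scored.** Study Time Points: the scores "will be assessed at T0, during the procedure (10 minutes from the start; T1), and immediately after the end of the procedure (T2"). During-procedure data exist from T1 and, with consent, from video.
4. **What is compared.** Statistical Analysis: Venham scores at T2. If the difference in score means change from T0, the endpoint is still T2.
5. **Whether T1 is compared elsewhere.** T1 does not appear in the analysis section. The statement that the two groups will be compared gives neither variable nor time point. Descriptive statistics by treatment might include T1 but are not a specified contrast. The video scores go to inter-judge agreement. Heart rate and oximetry during the procedure are secondary outcomes compared between groups, but they are not Venham scores.
6. **Why T2 may have been chosen.** Saliva is collected only at T0 and T2 (Study Time Points; Measurement of Salivary Amylase). T2 is thus the only time after baseline at which both parts of the composite exist.
7. **Whether T1 always exists.** Eligible procedures run from cleaning to extraction, and a procedure may be stopped when cooperation is impossible (Study Proceedings). One that ends before 10 minutes has no T1 as defined, and where anxiety caused the stop, that gap is informative. The article gives no durations, so the number of such children cannot be worked out.
8. **Whether T1 captures the peak.** The Introduction states that "the biggest trigger of DFA is the anticipation and use of local anesthesia injections". If an injection comes early, a single reading at 10 minutes can miss it. The article does not say when injections are given.
9. **Effect on alpha and sample size.** Assuming an overall level of .05, .05 / 2 = .025, which matches the stated alpha. If T1 replaces T2 as the anxiety contrast there are still two tests, so alpha stays at .025 and the sample at 20 (10% of 200). If T1 were added as a third Bonferroni test, alpha would be .05 / 3 = .0167.

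**The case against.** The strongest reply has four parts.

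**This is a condensed article about a 20-child feasibility pilot.** Recruitment, completion and satisfaction are the named primary outcomes, objective 3 seeks only preliminary effects, and T1 is collected anyway, so nothing is lost. This stands as regards severity. It does not remove the mismatch: the article does not leave the time point open but names T2, and an analysis plan that followed it would carry T2 forward.

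**T2 has a visible reason.** It is the only post-baseline time with both saliva and Venham scores. This stands, and it means that the anxiety contrast cannot move to T1 without being separated from the salivary part. It does not make T2 the right time for the stated objective.

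**During-procedure data are not ignored.** A reader might infer that T1 is the only anxiety score taken during the procedure, or that no during-procedure measurement is compared between groups. The documents support neither: the video evaluators also score anxiety during the procedure, and heart rate is compared during as well as after it. What holds is narrower: no during-procedure Venham score enters a named group comparison.

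**T1 has weaknesses of its own.** It may be absent in short procedures and may miss an early injection. Both are fair. They call for a rule and a supportive measure, not for a return to T2.

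**Conclusion.** The mismatch holds. The only specified between-group Venham comparison is made after the procedure, while the objective concerns the procedure itself. This rests on the article's own sections and on no numerical assumption.

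The size of the consequence cannot be derived. A reader might infer that T2 scores will sit near the floor of the 0–5 scale in both arms, that power at T2 is lower by a given amount, or that the later trial would be mis-sized by a given factor. The article gives no Venham distribution, effect size, standard deviation or share of the effect that persists to T2. It already expects 200 children in the later trial and states no rule for sizing that trial from the T2 effect. None of these claims should be attached to the point.

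Severity: should be fixed before analysis. Feasibility conclusions do not depend on it and the T1 data will exist, but as written a listed primary objective has no specified test that answers it.

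**What to change.** In Statistical Analysis:

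- Make the during-procedure Venham score (T1, adjusted for T0) the main anxiety contrast at the existing alpha of .025, and keep the T2 Venham score as secondary.
- Analyse the salivary marker separately at T2, where it is collected.
- Define T1 by one rule for every child. For example: the on-site rating at 10 minutes or, if the procedure ends sooner, the last on-site rating made during it.
- Report the highest during-procedure score for every child as a separate supportive measure. It should not stand in for T1 in short procedures only: that would mix a point score with a peak according to procedure length, which arises after randomization and is itself compared between arms. Take it from the on-site rating, because filming depends on consent.

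Cost: revised analysis wording and one field on the rating form. No extra staff or children are needed, and alpha is unchanged because T1 replaces T2 rather than joining it. The one loss is that anxiety and saliva are no longer a single T2 composite.
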